### Process measures

In this study, exercise done by the participant refers to those that are prescribed by the therapist. Both unsupervised (defined as exercise done by patient without physical presence of a therapist) and supervised exercise (defined as exercise done by patient in the physical presence of a therapist) that participants have performed are tracked during the trial for both intervention and control subjects. Adherence to supervised and unsupervised therapy will be recorded by the subject in a diary to record the number of minutes subject spent each day in therapy with a therapist (excluding time with the tele-therapist) and the number of minutes subject spent each day doing their prescribed rehabilitation exercises. The tele-therapist will check that the intervention subject is entering these data during tele-consultations. For the control (usual care) subjects, the Study Coordinator will call the subject every 4 weeks to check that the intervention subject is entering these data as well.

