**Methods/design:**

This is a single blind (evaluator blinded), parallel, two-arm randomised controlled trial study design involving 100 recent stroke patients. The inclusion criteria are age ≥40 years, having caregiver support and recent stroke defined as stroke diagnosis within 4 weeks. Consenting participants will be randomized with varying block size of 4 or 6 assuming a 1:1 treatment allocation with the participating centre as the stratification factor. The baseline assessment will be done within 4 weeks of stroke onset, followed by follow-up assessments at 3 and 6 months. The tele-rehabilitation intervention lasts for 3 months and includes exercise 5-days-a-week using an iPad-based system that allows recording of daily exercise with video and sensor data and weekly video-conferencing with tele-therapists after data review. Those allocated to the control group will receive usual care. The primary outcome measure is improvement in life task’s social activity participation at three months as measured by the disability component of the Jette Late Life Functional and Disability Instrument (LLFDI). Secondary outcome variables consist of gait speed (Timed 5-Meter Walk Test) and endurance (Two-Minute Walk test), performance of basic activities of daily living (Shah-modified Barthel Index), balance confidence (Activities-Specific Balance Confidence Scale), patient self-reported health-related quality-of-life [Euro-QOL (EQ-5D)], health service utilization (Singapore Stroke Study Health Service Utilization Form) and caregiver reported stress (Zarit Caregiver Burden Inventory).

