Given the current heterogeneity and room for improvements in solutions related to post-stroke rehabilitation, there is a need for well-designed intervention and rigorous trial to close the gap. The Singapore Tele-technology Aided Rehabilitation in Stroke (STARS) Study is a parallel, two-arm (intervention-control), single blind (evaluator-blind) randomised controlled trial to determine if a novel tele-rehabilitation intervention can improve functional recovery of post-stroke patients. For the tele-rehabilitation intervention arm of this study, the team developed small affordable lightweight wireless wearable sensors which can be strapped onto patients to allow real-time biofeedback and collection of sensor data from the sensors for subsequent transmission to patient’s rehabilitation team wirelessly via the internet. The sensor data is automatically summarized in chart form for quick review by therapist to allow them to prescribe further rehabilitation exercises remotely. The system also automatically allows the patient to self-record videos of them exercising which will also be transmitted to the therapist (termed ‘tele-therapist’) for review where needed, and allow patients and their therapists to communicate with each other using video-conferencing. The study’s primary hypothesis is that this novel tele-rehabilitation intervention during the first three months after stroke admission will result in greater functional recovery compared to usual care three months after stroke admission, as determined by the Jette Late Life Functional and Disability Instrument (LLFDI). Secondary hypotheses are that tele-rehabilitation intervention during the first three months after stroke admission will result in greater functional recovery as determined by gait speed, 2-min walk test and Shah modified Barthel Index, less health service utilization, greater contact time with therapist, better balance, better quality of life, less caregiver burden and be more cost-effective compared to usual care three months after stroke admission. Process measures in the form of a diary will be used to assess improved adherence in rehabilitation. Outcomes will also be assessed again at six months post-stroke to determine whether any improvement in outcomes is sustained in both groups.

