### Usual care

Stroke patients in Singapore typically receive acute stroke care in an acute hospital, which usually has a dedicated stroke unit. Those who are totally dependent or fully independent in activities of daily living (ADL) usually do not receive post-stroke rehabilitation. Those who are mild to moderately dependent in ADL are usually referred for centre-based rehabilitation after discharge from acute hospital. For those who are moderately to severely dependent in ADL, they usually receive inpatient rehabilitation for 4–6 weeks at inpatient rehabilitation hospitals after discharge from the acute stroke unit. These moderately to severely ADL dependent patients usually would have recovered to become mild to moderately ADL dependent during their inpatient rehabilitation hospitals stay, and hence would be referred for centre-based rehabilitation after being discharged home from inpatient rehabilitation hospitals. In acute hospitals, rehabilitation is usually started soon after stabilization of stroke and would be provided once a day for a total of 1–2 h a day by a physiotherapist and occupational therapist. In inpatient rehabilitation hospitals, rehabilitation is continued upon admission and would be provided twice a day for a total of 2–3 h a day by a physiotherapist and occupational therapist. After discharge, it usually takes 1–2 weeks for centre-based rehabilitation to be initiated and this is usually provided 1–2 times a week for an hour each time.

Home rehabilitation in Singapore is relatively under-developed and generally unavailable and unaffordable for the majority of stroke patients. Government subsidies for acute hospital and inpatient rehabilitation hospital stays are available, and government subsidies for centre-based rehabilitation are also available. However, government subsidies for home rehabilitation, previously unavailable, were only made available mid-way through this trial in July 2014.

It should be noted that for ethical reasons, the intervention group is allowed to supplement their tele-rehabilitation sessions with centre-based rehabilitation if they desire. To control for this at the data analysis stage, we will capture data on the total number of hours of use of centre-based and home rehabilitation for both intervention and control groups throughout the six months from study recruitment.

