### Outcome assessments

The primary outcome variable and the secondary outcome variables chosen for the study are based on the notion that patients undergoing rehabilitation are more concerned with their improvement in activities and participation instead of reducing their impairment [22]. Although many of the exercises prescribed in this study are known to only reduce impairment, the uses of the primary outcome variable and secondary outcome variables are still valid as the exercises prescribed also improve activity and participation. Furthermore, the participants are asked to walk as much as possible during the 3 months of tele-rehabilitation.

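### Diary minutes of prescribed exercise are to be read as adherence, but with no record of what controls were prescribed they mix the size of the prescription with compliance

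*Protocol article*

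**What the plan says.** The Background states that "Process measures in the form of a diary will be used to assess improved adherence in rehabilitation". Process measures then limits what counts: "exercise done by the participant refers to those that are prescribed by the therapist". It names two diary counts, both in minutes per day. One is time "in therapy with a therapist (excluding time with the tele-therapist"), which serves as the supervised measure. The other is "the number of minutes subject spent each day doing their prescribed rehabilitation exercises", which serves as the unsupervised measure. Neither count is paired with a prescribed amount.

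The two arms are described differently. The Abstract says the intervention "includes exercise 5-days-a-week using an iPad-based system". Table 2 lists walking as a functional activity with no upper limit, and Outcome assessments adds that "the participants are asked to walk as much as possible during the 3 months of tele-rehabilitation". For centre-based rehabilitation after discharge, Usual care says that "this is usually provided 1–2 times a week for an hour each time", after a start-up delay of 1–2 weeks. No home-exercise or walking prescription is described for controls.

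**The concern.** Minutes done are a dose. Adherence is what was done relative to what was asked. If one arm is asked to do more, it will record more minutes at the same compliance, and the diary cannot separate the two explanations.

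Walking sharpens the problem. In the tele-rehabilitation arm it is part of the prescribed programme and so can be entered as exercise. In the control arm it falls within the stated definition only if a therapist prescribed it.

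What is at stake is the interpretation of a process measure. The trial could report improved adherence under tele-rehabilitation when participants in both arms did the same share of what they were asked. A later analysis plan could not repair this, because a control denominator that was never collected cannot be rebuilt.

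**Working it through.** The plan states no figure for this measure, so there is nothing to reproduce. The check uses the described schedules.

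**Inputs from the protocol article**
- Tele-rehabilitation: 5 exercise days a week (Abstract, Methods/design). Minutes per session are not stated.
- Usual care after discharge: 1–2 centre sessions a week of one hour each (Usual care). A home prescription is not stated.

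**Step 1: what the documents show about frequency.** The ratio of scheduled sessions is 5/2 = 2.5 to 5/1 = 5. This is a difference in frequency, not in minutes. The control's 60–120 min/week is time with a therapist present and belongs to the supervised count, so it must not be set against tele home-exercise minutes.

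**Step 2: unsupervised minutes at equal compliance.** Let c be the common compliance, T the weekly tele prescription and C the weekly control home prescription, both in minutes. Recorded minutes are cT and cC, so

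difference = c × (T − C).

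The ratio of minutes done to minutes prescribed is c in each arm, a difference of 0 whenever T and C are above zero.

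**Step 3: illustration.** Session length, c and C are all assumptions. Walking is left out. With c = 0.5:

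| Assumed tele session | T (min/week) | C = 0 | C = 60 | C = 100 | C = 150 |
|---|---|---|---|---|---|
| 20 min | 5 × 20 = 100 | 50 | 20 | 0 | −25 |
| 30 min | 5 × 30 = 150 | 75 | 45 | 25 | 0 |
| 60 min | 5 × 60 = 300 | 150 | 120 | 100 | 75 |

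Cells are the tele excess in min/week. For example, 0.5 × (150 − 60) = 45. At T = 150 and C = 0, the excess is 0.3 × 150 = 45 for c = 0.3 and 0.8 × 150 = 120 for c = 0.8. The artefact vanishes only where C = T, and it reverses where C exceeds T.

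**Step 4: walking.** Suppose 20 min a day is walked and entered as prescribed exercise. That adds 20 × 7 = 140 min/week to a tele participant's record. The same walking adds nothing for a control with no walking prescription, and the same 140 min/week for a control who has one. The 20 minutes is an assumption, and the article does not say how participants will log ordinary walking.

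**Step 5: the supervised count.** Time with the tele-therapist is excluded, so the weekly video consultation adds 0 minutes. The tele programme cannot raise this count. If home sessions replace centre visits, the count moves against tele-rehabilitation.

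**The case against.** A reader might infer that the whole adherence comparison favours tele-rehabilitation by construction. The documents do not support that. The supervised count excludes tele-therapist time and may run the other way, and it is the one the Discussion uses when it asks whether any benefit is due to better adherence to supervised exercise.

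Nor do the documents show that controls are prescribed little or nothing at home. Control therapists may prescribe exercise or walking, and it would then count. The 20.3% adherence at 3 months cited in the Background describes an earlier group of patients; low uptake of a recommendation does not show that none was given. The share of recommended time used there also belongs to a cited cohort, so it does not contradict this trial's definition.

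It would also go too far to say that a formal hypothesis becomes untestable. The Background's primary and secondary hypotheses do not include adherence, and it is not among the seven listed secondary outcomes. Effects on gait speed and walk distance rest on the randomised comparison, not on the diary.

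Finally, the tele system does hold prescriptions (Software component, Tele-therapist interface), and Usual care promises hours of centre-based and home rehabilitation in both arms. The first covers the intervention arm only, and the second is service use, not exercise prescribed. A ratio also has limits: it has no denominator for open-ended walking and is undefined for anyone without a prescription.

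These points narrow the concern to the unsupervised count. They do not remove it, because that count is still labelled adherence and no control denominator is described.

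**Conclusion.** The concern holds for one process measure. Diary minutes of prescribed exercise combine the amount prescribed with compliance, so a between-arm difference can appear as improved adherence when compliance is equal. The direction favours tele-rehabilitation if its participants are prescribed more unsupervised exercise than controls. The described schedules and the open-ended walking make that plausible but do not establish it.

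The size cannot be fixed from the article. The 75-to-0 min/week range depends on assumed 30-minute sessions, 50% compliance in both arms and control home prescriptions of 0 to 150 min/week, and it excludes walking. The supervised count, the primary outcome and the seven listed secondary outcomes are not affected. This is worth correcting because correction is cheap and the missing denominator cannot be recovered afterwards.

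**What to change.** 1. Report raw diary minutes in both arms as exercise dose, not adherence, and keep supervised and unsupervised minutes separate.
2. Give walking its own diary line for every participant, whether or not a therapist prescribed it.
3. Record the weekly prescribed amount in both arms, in minutes: from the tele-therapist application for the intervention arm, and by a question at the existing 4-weekly coordinator call for controls.
4. Report minutes done over minutes prescribed, leaving out open-ended walking, as a descriptive adherence measure. Show participants with no prescription as a separate category.

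The cost is a slightly longer diary and call. The ratio exists only for participants with a prescription, a subset that can differ between arms after randomisation. It should therefore stay descriptive and sit beside the dose in minutes, which is defined for everyone. Step 1 alone costs nothing and already prevents a misleading statement about adherence.

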### Feedback

For intervention participants, feedback about their rehabilitation progress is given via real-time and Facetime. For real-time biofeedback, visual and audio feedback is given to the participant through the iPad for every repetition that exceed the target angle when the participant is performing the rehabilitation exercises. For Facetime, the tele-therapist will have a face-to-face consultation with the participant via video call once a week. They will evaluate the participant based on the data collected from the sensors (which capture the progress of the participant when he/she performs the rehabilitative exercises), and the exercises which the participant may be asked to perform during the video call.

### Outcome assessments

The primary outcome variable and the secondary outcome variables chosen for the study are based on the notion that patients undergoing rehabilitation are more concerned with their improvement in activities and participation instead of reducing their impairment [22]. Although many of the exercises prescribed in this study are known to only reduce impairment, the uses of the primary outcome variable and secondary outcome variables are still valid as the exercises prescribed also improve activity and participation. Furthermore, the participants are asked to walk as much as possible during the 3 months of tele-rehabilitation.

#### Primary outcome variable

Functional ability may be quantified using performance based measures or self-report. Self-report measures remain the most commonly used instruments in many studies involving older adults because of their low cost and practicality [23]. Disability component of the Jette LLFDI, a self-reported measure of social activity participation in life tasks, was selected as the primary outcome measurement for this study, as the same outcome measure was used in a similar tele-rehabilitation study done by Chumbler et al. [13]. The LLFDI will be administered by research assistants. The disability component evaluates self-reported limitations in life activities and frequency of participation in 16 major life tasks categorized under 4 main roles (instrumental, management, social and personal). The degree of limitation and frequency dimensions of each life task are scored on a 0–100 scale, with higher scores indicating higher levels of functioning. The disability component has shown concurrent validity by correlating with the Physical Functioning (PF-10) subscale of the Medical Outcomes Study 36-item Short-Form Health Survey and the London Handicap Scale [24].

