### Statistical analysis

#### Sample size

Chumbler et al’s paper had similar tele-rehabilitation intervention at 0, 3 and 6 months, and the same primary outcome measure, the Difficulty dimension of the Disability component of the Jette LLFDI [12]. Even though the mean score derived from the results in Chumbler et al’s paper was 11 [12], a mean score of 8 was used in this study due to different geographical and socio-cultural context; Chumbler et al’s study was done in the United States whereas this study was done in Singapore, where rehabilitation is less well-accepted. Hence, based on a two-sided test of 5 % and a power of 90 %, and assuming a difference in mean scores of 8 and a standard deviation of 16, and a correlation of 0.6, a total sample size of around 86 (intervention = 43, controls = 43) was calculated to be adequate. Accounting for 14 % attrition rate, the minimum sample size was determined to be 100 (intervention = 50, controls = 50). It is planned that 100 participants will be recruited within 2 years, after which an additional 6 months is needed for follow-up.

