#### Analysis for outcome measures

Data entered will be checked for accuracy at least twice by at least two independent assessors. To understand the structure of missing data and to reduce bias from uncertainty of missing data, multiple imputations will be performed using the Markov Chain Monte Carlo method. All scale-based measures used in this study will be screened via an internal consistency test (Cronbach’s alpha test) before creating a summative score. Furthermore, rigorous validity tests will be performed in two ways: person-centered tests (latent class analysis) and variable-centered tests (exploratory and confirmatory factor analyses).

For descriptive statistics, independent two-sample *t*-test and Analysis of Covariance (ANCOVA) will be performed on all continuous outcome measures (i.e. Shah-modified BI, ABC Scale, gait speed, two-minute walk test and ZBI) between tele-rehabilitation vs. usual care group if outcomes are normally distributed. Mann–Whitney *U* test will be performed on data with skewed distribution to test differences between treatment groups. Chi-square test will be performed on categorical variables. Confounders are age, gender, ethnicity and marital status. Multiple linear regressions will be used to adjust for differences in confounders between intervention and control groups for continuous outcome variables. Ordered logistic regressions will be used to adjust for differences between intervention and control groups for continuous categorical variables. For these multivariate linear and logistic regressions, we will use survey analysis processes with robust standard errors which accounts for nesting effects within patient data as a result of clustering by different recruitment centers. For all statistical analyses, the level of significance (α) will be taken at 0.05. Analyses will be based on the intention-to-treat approach. We will use STATA version 12 for statistical analysis and significance level is set at P < 0.05.

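### The primary LLFDI score is named inconsistently, is missing from the list of outcomes to be tested, and has no designated deciding test

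*Protocol article*

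**What the plan says.** **The variable.** Four places describe it.

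- Background (primary hypothesis): functional recovery "as determined by the Jette Late Life Functional and Disability Instrument (LLFDI"). No component or dimension is named.
- Abstract, Methods/design: "The primary outcome measure is improvement in life task’s social activity participation at three months as measured by the disability component". No dimension is named.
- Primary outcome variable: the disability component, covering limitations in life activities and frequency of participation. "The degree of limitation and frequency dimensions of each life task are scored on a 0–100 scale". Neither dimension is selected, and no rule for combining them is given.
- Sample size: the cited tele-rehabilitation study is said to have "the same primary outcome measure, the Difficulty dimension of the Disability component of the Jette LLFDI". That label does not appear in the outcome section.

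The time point, 3 months, is fixed.

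**The analysis.** Under Analysis for outcome measures, the t-test and ANCOVA apply to "all continuous outcome measures (i.e. Shah-modified BI, ABC Scale, gait speed, two-minute walk test and ZBI"), provided the data are normally distributed. For other data, a Mann–Whitney "test will be performed on data with skewed distribution to test differences between treatment groups". Multiple linear regression then adjusts continuous outcomes for confounders, given as age, gender, ethnicity and marital status. The significance level is 0.05 throughout, and no analysis is called primary.

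**Baseline.** Table 1 under Baseline assessments does not list the LLFDI. The Quality of life section says specifically that the EQ-5D is also given at baseline. No such sentence exists for the LLFDI.

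**The concern.** A trial with one confirmatory claim needs one variable and one test, recognisable under the same name wherever they appear. Here a reader cannot tell which 0–100 score is primary, and the section that should say how it is tested lists other outcomes instead. If the choice is left open until results are seen, the nominal 5% level no longer describes the chance of a false claim. The sample size assumes a difference of 8 points with a correlation of 0.6. A correlation matters only if repeated measurements enter the analysis, yet the analysis section does not name baseline score as a covariate.

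**Working it through.** **1. Can the sample size reveal the intended test?** Inputs from the Sample size section: difference 8, SD 16, correlation 0.6, two-sided 5%, power 90%, 86 evaluable, 14% attrition.

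Per arm, n = 2(1.960 + 1.282)² × 16² × f / 8² = 84.06 × f, where f is the variance factor for the analysis.

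| Analysis at 3 months | f | Per arm | Total |
|---|---|---|---|
| Post score only (t-test) | 1 | 85 | 170 |
| Change score | 2(1 − 0.6) = 0.80 | 68 | 136 |
| ANCOVA on baseline | 1 − 0.6² = 0.64 | 54 | 108 |

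None gives 86. The attrition step does reproduce: 86 / (1 − 0.14) = 100. So the primary test cannot be inferred from the sample size. The gap in the sample size is a separate matter and is not argued here.

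**2. Is the LLFDI in the analysis section?** The closed list reads "i.e. Shah-modified BI, ABC Scale, gait speed, two-minute walk test and ZBI". All five are among the seven secondary outcomes. The list also lacks the EQ-5D, so it looks incomplete rather than deliberately restricted. The regression sentence refers to continuous outcome variables without a list and can be read to include the LLFDI.

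**3. Two dimensions, if either could be claimed at two-sided 5%.** The false-positive rate is 1 − P(|Z₁| ≤ 1.96 and |Z₂| ≤ 1.96) for a bivariate normal. With independence this is 1 − 0.95² = 9.75%. The correlation between dimensions is not in the article, so the other rows are assumptions. The 0.6 in the sample size is not described as a correlation between dimensions.

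| Assumed correlation | False-positive rate |
|---|---|
| 0 | 9.8% |
| 0.3 | 9.5% |
| 0.6 | 8.7% |
| 0.8 | 7.8% |
| 0.9 | 7.0% |

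**4. One score, if either the t-test or ANCOVA could be claimed.** With baseline correlation 0.6, the two test statistics correlate at about √(1 − 0.36) = 0.8 under the null. By the formula in step 3 this gives 7.8%. Simulation with 43 per arm, normal data and 10,000 null trials gives 7.7%. Allowing Mann–Whitney as a third option gives 8.4%.

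**5. The normality switch alone.** A t-test or Mann–Whitney was chosen by a Shapiro test on pooled residuals, with 43 per arm and 40,000 null trials. The false-positive rate was 4.9% for normal, 5.1% for lognormal and 5.2% for exponential data. The switch adds little error. The inflation in step 4 comes from running several analyses without ranking them.

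**The case against.** The best defence is that one score was intended. The sample size section speaks of a single dimension, and an analysis plan that is not shown may name the test. Four stronger readings are tempting, and the article does not support them.

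- **That the trial has two primary scores and may succeed on either.** No section says so. The sample size points to one dimension. The defect is that the endpoint definition does not carry that choice and the names do not match.
- **That the primary outcome has no analysis at all.** The regression sentence can cover it. It would also still give a difference in points if the data were skewed.
- **That the switch to Mann–Whitney inflates the error rate.** Step 5 shows that it stays near 5%.
- **That Difficulty simply means limitation.** This is plausible, but the article does not say so, and only the sponsor can settle it.

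The appeal to a later analysis plan answers only part of the point. Choosing among stated tests is often left to such a plan. Conflicting names for the primary variable and a closed list without it are statements in this document, and they need correcting here.

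**Conclusion.** The concern holds in this form: the primary variable has inconsistent names, the list of tested outcomes omits it, and several tests at 0.05 stand side by side with none decisive. The naming conflict and the omission can be read directly from the text.

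The error rates are conditional. The range of 9.8% to 7.8% requires that either dimension may be claimed, with an assumed correlation of 0 to 0.8. The figure of about 7.7% requires that either the t-test or ANCOVA may be claimed for one score, with baseline correlation 0.6. The article does not say that either will happen, but it contains nothing that rules them out. Naming one score and one test restores the 5% level without changing the number of participants.

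Whether a baseline LLFDI exists is unresolved. Improvement as an outcome and the correlation in the sample size imply one, but Table 1 does not show it.

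**What to change.** 1. The sponsor identifies which dimension the sample size figures refer to and uses that one name in the abstract, Background, Primary outcome variable, Sample size and Analysis for outcome measures. The other dimension becomes secondary.
2. Add the LLFDI to the analysis section with one primary test at two-sided 5%: ANCOVA of the 3-month score on treatment, baseline score and site (the stratification factor). Keep it whatever the distribution, with robust or bootstrap standard errors if the data are skewed. The t-test, Mann–Whitney and confounder-adjusted regression become sensitivity analyses.
3. Add the LLFDI to Table 1, or confirm that it is already collected at baseline.

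Cost: the first two are text changes, and they give up a second chance of success. The third costs one short questionnaire per participant if it is not already collected. The Usual care section refers to an event midway through the trial, so a baseline score that was never taken could not be recovered for those already enrolled. The sponsor should therefore settle this first. All three should be settled before any unblinded data are seen.
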